## Abstract

**Introduction:**

The transition from child and adolescent mental health services (CAMHS) to adult mental health services (AMHS) represents a critical period of vulnerability, often marked by care discontinuities and adverse clinical outcomes. International studies have highlighted the risks associated with this transition, but local epidemiological data remain scarce in France. The Odyssée study aims to provide local data to inform the development of structured transition pathways.

**Methods and analysis:**

This prospective monocentric cohort study will be conducted at Lenval University Children’s Hospital in Nice, the only paediatric hospital providing dedicated child psychiatry emergency services in the Alpes-Maritimes department. Recruitment started in April 2026 and is ongoing at the time of manuscript submission. Study completion is anticipated in September 2028. The primary objective is to determine the annual prevalence of 17-year-olds living in Nice who attend child and adolescent psychiatry services using administrative data combining census counts from the French National Institute of Statistics and Economy Studies and hospital discharge records (*Programme de médicalisation des systèmes d’information* (PMSI)).

In parallel, a prospective cohort of 100 adolescents aged 17 years will be followed for 12 months to address secondary objectives, including clinical profiles, care trajectories, transition readiness, clinical outcomes and determinants of care continuity. Assessments will be conducted at baseline, 6 months and 12 months using validated instruments (Mini International Neuropsychiatric Interview—simplified (MINI-S), WHO Quality of Life-brief (WHOQOL-BREF), Health of the Nation Outcome Scales for Children and Adolescents (HoNOSCA), Transition Readiness and Appropriateness Measure (TRAM), Transition Related Outcome Measure (TROM)). Descriptive and multivariable analyses will be performed to identify factors associated with continuity of care. This study is expected to provide one of the first city-level estimates of psychiatric transition needs in France and contribute to the international literature on continuity of care, youth mental health trajectories and transitional service organisation.

**Ethics and dissemination:**

The study has been approved by the Comité de Protection des Personnes Sud-Ouest et Outre-Mer IV (approval number 2025-A01581-48). Written informed consent will be obtained from participants and one parent or legal guardian. Findings will be disseminated through peer-reviewed publications, scientific conferences and reports to regional health authorities.

**Trial registration number:**

NCT07068945.

STRENGTHS AND LIMITATIONS OF THIS STUDYDual-source design combining administrative data (French National Institute of Statistics and Economy Studies/*Programme de médicalisation des systèmes d’information* (PMSI)) with prospective longitudinal follow-up.Standardised validated instruments (Mini International Neuropsychiatric Interview—simplified (MINI-S), WHO Quality of Life—brief (WHOQOL-BREF), Health of the Nation Outcome Scales for Children and Adolescents (HoNOSCA), Transition Readiness and Appropriateness Measure (TRAM) and Transition Related Outcome Measure (TROM)) are administered repeatedly over 12 months.Consecutive recruitment includes adolescents receiving outpatient, inpatient and emergency psychiatric care.The monocentric cohort design and sample size (n=100) may limit external generalisability.Attrition over 12 months may introduce bias if loss to follow-up is associated with clinical severity or care disengagement.

## Introduction

 The period between adolescence and adulthood is marked not only by physiological change but also by psychological vulnerability.^1^ Psychiatric disorders emerge before the age of 15 in 50% of cases and before the age of 25 in 75% of cases.^2
3^ In 2024, the WHO reported that 14% of individuals aged 10–19 years’ experience a mental health disorder, and suicide is the third leading cause of death among those aged 15–29 years.^4^ The transition from adolescence to adulthood is therefore a critical period both for the detection of emerging psychiatric disorders with high risk for chronicity and for ensuring continuity of care between child and adolescent mental health services (CAMHS) and adult mental health services (AMHS).^5^ This represents both an individual-level challenge, in terms of prognosis and quality of life, and a major public health issue at the societal level.^6
7^

Despite this, the organisation of care transfer from CAMHS to AMHS remains problematic. Approximately 60% of patients experience a disruption in care between child and adult psychiatry services,^8^ with an average treatment gap of about 3 months.^9^ Studies also show that 50% of patients followed in child psychiatry discontinue care altogether,^10
11^ and such discontinuity increases the risk of hospitalisation in adulthood by 20–30%.^12^ Moreover, the assessment and management of emerging psychiatric disorders in this age group, which are often transdiagnostic and non-specific, highlight the need for targeted training of healthcare professionals and adapted services.^13
14^ Barriers to access and the specific needs of this vulnerable population remain major obstacles to implementing a clear and coordinated care pathway for patients and their families.^15–18^

Transitional psychiatry refers to the practices, structures and supports designed to ensure continuity of psychiatric care between CAMHS and AMHS during the passage to adulthood.^6^ Several studies have characterised this population and highlighted the high frequency of care disruptions, the importance of early identification of young people at risk of disengagement and the need for structured protocols and dedicated teams to improve continuity and adherence.^19–23^ Importantly, discontinuity of care during this transition period has also been associated with increased risk of adverse outcomes, including hospitalisation, relapse and premature mortality, particularly in young people with severe mental disorders.^10^ Most of these studies have relied on multicentre methodologies^20
24^ or focused on specific dedicated units,^25^ but there is little evidence from local or city-level research.

Beyond organisational challenges, the transition from CAMHS to AMHS also reflects a broader developmental and epidemiological issue.^5
6^ Administrative age boundaries do not necessarily correspond to the trajectories of emerging psychiatric disorders, which often evolve across adolescence and early adulthood.^3
15^ Young people approaching the transition boundary represent a heterogeneous population, characterised by varying clinical presentations, psychosocial vulnerabilities and patterns of service use.^13
15
18^ In this context, local epidemiological studies conducted in real-world settings may contribute to the international literature by improving understanding of the needs and care trajectories of young people requiring ongoing psychiatric support during the transition to adulthood.^22
23^

Our study, Odyssée, is a local research project supported by the Regional Health Agency Provence-Alpes-Côte d’Azur. This prospective longitudinal cohort study adopts a city-level approach in Nice, linking child psychiatry administrative data with individual clinical follow-up to assess transition needs and inform specialised care pathways. The study will evaluate the transition from CAMHS to AMHS among 17-year-old adolescents living in Nice.

## Objectives

The primary objective of this study is to determine the annual prevalence of 17-year-old patients living in the city of Nice who consult specialised CAMHS child and adolescent psychiatry services, relative to the total population of 17-year-olds residing in Nice.

The secondary objectives are to:

Estimate the annual prevalence of 17-year-olds living in Nice who consult specialised CAMHS (Nice University Children’s Hospital(HPU Lenval)), relative to the population of minors (<18 years) in psychiatric clinical care.Describe the clinical and sociodemographic profiles of a sample of 17-year-old patients living in Nice and consulting specialised CAMHS (HPU Lenval).Characterise care trajectories over a 12-month follow-up period, according to the evolution of clinical management.Assess the clinical course of patients during follow-up.Evaluate the level of readiness for transition to adult psychiatry.Identify factors associated with continuity of psychiatric care at 12 months.

Taken together, these objectives aim to generate actionable local evidence to tailor transition planning and service organisation to the specific needs of young people in Nice. Findings will inform locally adapted tools and dedicated pathways to improve continuity of care across the CAMHS–AMHS transition.

## Methods and analysis

### Study design

The study includes two components:

An epidemiological analysis estimating the annual prevalence of 17-year-olds living in Nice who attend specialised CAMHS, using French National Institute of Statistics and Economy Studies (INSEE) census counts (population denominator) and *Programme de médicalisation des systèmes d’information* (PMSI) hospital discharge data from Lenval University Children’s Hospital (clinical numerator).A prospective monocentric cohort of 100 adolescents aged 17 years receiving psychiatric care at Lenval University Children’s Hospital, followed for 12 months with assessments at baseline, 6 months and 12 months.

The overall study duration is 36 months (18-month recruitment, 12-month follow-up and 6-month analysis). The overall study duration is approximately 30 months. Recruitment started on 7 April 2026 and is ongoing at the time of manuscript submission. Participant inclusion is planned over an 18-month period. Primary completion and overall study completion are both anticipated in September 2028, in accordance with the ClinicalTrials.gov, registration: NCT07068945.

### Eligibility criteria

Eligibility criteria are defined as follows:

#### Inclusion criteria

Participants must meet all of the following criteria:

Age ≥17 and <18 years at inclusion.Receiving care (outpatient, inpatient or emergency) within the Child and Adolescent Psychiatry Department at Lenval University Children’s Hospital.Presence of a psychiatric disorder according to Diagnostic and Statistical Manual of Mental Disorders, Fifth Edition (DSM-5) criteria, irrespective of diagnostic category.Considered to be in a potential transition situation to adult mental health services within the following 12 months.Living in the municipality of Nice (postal codes 06000, 06100, 06200, 06300).Able to provide written informed consent, together with at least one parent or legal guardian.

#### Exclusion criteria

Participants meeting any of the following criteria will be excluded:

Insufficient command of French preventing comprehension of study information or completion of questionnaires.Cognitive or sensory impairments (eg, moderate-to-severe intellectual disability, major visual impairment, severe reading difficulties) preventing valid completion of assessments.Legal incapacity (eg, guardianship) preventing independent consent.Acute or unstable clinical condition requiring urgent or intensive care incompatible with research participation (eg, severe psychiatric decompensation, immediate suicidal crisis).Refusal to participate by the adolescent or the parent(s)/legal representative(s).Any situation judged by the investigator as incompatible with 1 year follow-up (eg, imminent transfer to another region).

Withdrawal criteria

Withdrawal of consent by the adolescent or the legal representative(s).

### Recruitment and informed consent

Eligible adolescents and their parents or legal guardians will receive written and oral information about the study from a member of the research team who is not directly involved in the patient’s clinical care. Potential participants are identified consecutively by clinicians within the Child and Adolescent Psychiatry Department during routine outpatient consultations, inpatient admissions, day hospital care or emergency psychiatric assessments. Screening logs are maintained to document the number of eligible patients approached, included or refusing participation during the recruitment period. To ensure voluntary participation, a minimum 72-hour reflection period will be respected between information and consent. At inclusion (age 17), written informed consent will be obtained from at least one parent or legal guardian, together with the adolescent’s written assent. In accordance with French regulations governing minimal-risk interventional research involving minors, parental consent remains mandatory until participants reach the age of 18 years. When participants turn 18 during follow-up, renewed written consent will be obtained to continue participation. Participation or refusal will have no impact on clinical care, and withdrawal is possible at any time without consequences.

### Study procedures

The study comprises two complementary components:

Prevalence study (administrative data). 

Annual prevalence will be calculated for 17-year-olds living in the municipality of Nice who receive care in child and adolescent psychiatry services at the University Children’s Hospital, regardless of care setting, including inpatient admissions, day hospital care, scheduled outpatient consultations and emergency psychiatric assessments.

Population denominator:

The number of 17-year-olds living in Nice will be obtained from the most recent INSEE census data available (2022). Given the very small year-to-year variation in population counts for this age group, the 2022 figure will be used as the reference denominator for estimating 2025/2026 prevalence.

Clinical numerator:

Hospital utilisation data will be obtained from the PMSI system at Lenval University Children’s Hospital for the year 2024, which is the most recent complete dataset available at the time of analysis. These data will provide the number of 17-year-olds living in Nice who accessed child and adolescent psychiatry services, as well as the total number of minors (<18 years) receiving psychiatric care during 2024.

Longitudinal cohort study: 

A cohort of 100 adolescents aged 17 years will be prospectively recruited and followed for 12 months at a University Children’s Hospital. Three study visits are planned: baseline (V0), 6 months (V1) and 12 months (V2). Follow-up assessments at V1 and V2 are conducted irrespective of whether participants have turned 18 during the study.

Baseline (V0): After written informed consent is obtained from the adolescent and a parent/legal guardian, the participant will meet with a trained evaluator (principal investigator or delegated clinician) who will explain the study procedures, address any questions and introduce the assessment tools. This brief clinical interview (≈20–30 min) is not a medical examination and involves no clinical intervention; it may be conducted on site or via secure teleconsultation.Participants will then complete the baseline assessments, including:Collection of sociodemographic and medical information.Assessment of psychiatric symptoms and diagnoses (Mini International Neuropsychiatric Interview—simplified (MINI-S)).Evaluation of quality of life (WHO Quality of Life—brief (WHOQOL-BREF)) and care needs/psychosocial difficulties (Health of the Nation Outcome Scales for Children and Adolescents (HoNOSCA)).Assessment of readiness for transition (Transition Readiness and Appropriateness Measure (TRAM)).6-month follow-up (V1): Assessments will include:MINI-S.WHOQOL-BREF.HoNOSCA.TRAM.12-month follow-up (V2): Assessments will include:MINI-S.WHOQOL-BREF.HoNOSCA.Evaluation of transition outcomes using the Transition Related Outcome Measure (TROM).

The schedule of enrolment, assessments and follow-up is presented in figure 1. Study participation will end after the 12-month follow-up. Patients will continue to receive routine clinical care according to current recommendations and individual clinical needs.

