## Discussion

This study has several strengths. Its prospective longitudinal design focuses on a critical developmental stage, while the use of validated assessment tools (MINI-S, WHOQOL-BREF, HoNOSCA, TRAM, TROM) ensures methodological rigour and comparability with international work. By combining administrative data (INSEE, PMSI) with individual clinical follow-up, the study will provide a comprehensive picture of transition needs across all public child psychiatry services in a large French city.

Importantly, the study will address a gap in French epidemiology by providing the first city-level estimate of the annual prevalence of 17-year-olds accessing specialised CAMHS. This is essential for quantifying service needs at the transition boundary and informing resource planning. Although based on PMSI 2024 data, it offers a robust 1-year snapshot based on routinely collected administrative records; year-to-year variability cannot be assessed within the present dataset.

Some limitations must be acknowledged. The single-centre design and modest sample size (n=100) may restrict generalisability and limit the power of multivariable analyses. Anticipated loss to follow-up at 12 months also reflects the challenges inherent in transitional psychiatry.^21^ In addition, the absence of a control group or multicentre setting constrains external comparisons.

Although young people and parents were not directly involved in the design of this protocol, their needs and concerns routinely observed in clinical practice strongly informed the choice of outcomes and follow-up procedures. Adolescents and families frequently express anxiety regarding the transition to adult services, including fears of losing established therapeutic relationships, uncertainty about the functioning of adult-oriented services and concerns about changes in parental involvement after the age of 18. Clinicians also observe that periods of educational, social or familial instability may increase the risk of disengagement from care, particularly among young people with evolving or non-stabilised psychiatric presentations. These observations are broadly consistent with the international literature^5
6

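### The primary estimate is labelled 2025/2026 prevalence, but its numerator is a 2024 patient count and its denominator a 2022 census count

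*Protocol article*

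**What the plan says.** Two adjacent paragraphs of Study procedures (prevalence component) fix the years. The denominator is the 2022 INSEE count, defended by the phrase "Given the very small year-to-year variation in population counts for this age group", and the sentence ends by saying that "the 2022 figure will be used as the reference denominator for estimating 2025/2026 prevalence". The numerator paragraph then states "Hospital utilisation data will be obtained from the PMSI system at Lenval University Children’s Hospital for the year 2024", with the reason "which is the most recent complete dataset available at the time of analysis".

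Primary outcome (under Outcomes) defines the measure as the 17-year-olds seen in one year over all 17-year-olds resident in Nice, without naming the year. Study design gives 7 April 2026 as the start of recruitment and adds: "Primary completion and overall study completion are both anticipated in September 2028". The Discussion describes the estimate as a one-year snapshot from PMSI 2024 and says that "year-to-year variability cannot be assessed within the present dataset".

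**The concern.** A period prevalence belongs to the period in which the patients were counted. Here the count comes from 2024 and the label says 2025/2026. No PMSI extraction for 2025 or 2026 is planned anywhere in the article. The label is therefore a projection that assumes unchanged service use after 2024, and the Discussion says the dataset cannot check that assumption.

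The reason given for choosing 2024 adds to the difficulty. It rests on what is available when the analysis is done, but the stated calendar places completion well after 2025 and 2026 have ended.

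This is the only primary outcome. The Discussion presents it as a first city-level figure for quantifying service needs and planning resources. A planner who reads 2025/2026 would take it as demand measured in those years.

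**Working it through.** **Years entering the estimate**

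| Element | Year | Justification in the article |
|---|---|---|
| Label (Study procedures, denominator paragraph) | 2025/2026 | none |
| Denominator, INSEE | 2022 | latest census available; little variation in population counts |
| Numerator, PMSI | 2024 | latest complete year at analysis |
| Discussion | 2024 snapshot | year-to-year change not assessable |

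The population argument links 2022 to later years for the denominator. No statement links 2024 to 2025/2026 for the numerator.

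**Calendar** (inputs from Study design: start 7 April 2026, 18 months of inclusion, 12 of follow-up, 6 of analysis)

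- End of inclusion: 7 April 2026 + 18 months = 7 October 2027.
- End of follow-up: + 12 months = 7 October 2028, close to the stated September 2028.
- End of analysis: + 6 months = 7 April 2029.
- From the end of 2024 to the start of recruitment: about 15 months. Calendar year 2025 had then been over for about 3 months.
- From the end of 2024 to September 2028: about 44 months. From the end of 2025 to September 2028: 44 − 12 = 32 months.

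So if the prevalence analysis were run at the stated primary completion, 2024 would be the latest complete year only if PMSI 2025 were still incomplete 32 months after that year closed. Study design gives the total duration both as 36 months and as about 30 months; this check does not depend on which is right.

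**How much the year of each count could matter**

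The article gives no prevalence, no INSEE count and no PMSI count for Nice residents, so there is no figure to reproduce. With prevalence = n/D:

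- Numerator: Sample size estimation gives about 160 to 200 patients aged 17 per year. For any D, the ratio is (200/D)/(160/D) = 200/160 = 1.25.
- Illustration with an assumed D of 3,500 (not in the article) and exact 95% limits: 160/3,500 = 4.57% (3.90 to 5.32); 200/3,500 = 5.71% (4.97 to 6.54). With D assumed anywhere from 2,500 to 4,500, the estimate runs from 160/4,500 = 3.56% to 200/2,500 = 8.00%.
- Denominator: if the true population differs from the 2022 count by a fraction g, the relative change in prevalence is 1/(1+g) − 1. For g = +1% this is −1.0%, for g = +5% it is −4.8%, and for g = −5% it is +5.3%. These values of g are hypothetical.

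The numerator year is therefore the more influential of the two, and it is the one whose transfer to 2025/2026 is not argued.

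**The case against.** The label 2025/2026 occurs once, in the denominator sentence. The objectives, the outcome definition and the analysis section do not repeat it, and the Discussion names PMSI 2024 openly. On that view this is one loose phrase in an otherwise disclosed snapshot. That stands as far as disclosure goes, and it makes the repair small. It does not remove the contradiction, because that sentence is the only one that says which period the primary estimate is meant to describe.

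A reader might infer that 2024 will certainly not be the latest PMSI year at analysis. The documents do not establish this. They give no PMSI closing lag and no date for the prevalence analysis. The database lock under Data management concerns data entered in the electronic case report form, and the prevalence component could be run early. What stands is that the stated reason fits the stated calendar poorly and needs a date or an explanation.

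A reader might also infer that the denominator is invalid because nobody aged 17 in 2022 was still 17 in 2024. The age arithmetic is right, but the 2022 count serves as a proxy for population size, not as a list of the same people. Nothing in the article contradicts the premise of small variation. Substituting a younger census row would not settle the matter either: people aged 17 at some time in one calendar year come from two birth years, and some move into or out of Nice in between.

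Finally, a reader might conclude that several years must be pooled for precision. The objective is an annual prevalence, which a single year answers. A gain computed from pooled counts would be unreliable, because a patient can be 17 in two adjacent calendar years and be counted twice.

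**Conclusion.** The point holds as an inconsistency in the period of the primary estimate. The data planned are 2024 patients over a 2022 population; the label is 2025/2026; and the article offers no basis for moving the patient count forward. The choice of 2024 is also inadequately explained against a calendar that runs to September 2028, although whether a later PMSI year will be complete at the time of the analysis remains an inference.

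The error in prevalence cannot be calculated, because neither count is given. The factor of 1.25 shows what a change within the protocol's own annual range would do. It is illustrative: the 160 to 200 is approximate, is not stated to be restricted to Nice residents, and is not presented as a measure of year-to-year change. The denominator lag alone is minor, and it is disclosed and argued for. The consequence is for interpretation: as labelled, the primary result would claim a period that it did not observe.

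**What to change.** Take one of two routes.

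1. Keep 2025/2026 as the target. Repeat the same PMSI query for each calendar year that is complete when the analysis is run, including the years in the label, and report each year's prevalence under its own year. The cost is a repeated query, a short amendment and possibly a slightly later primary result.
2. Keep 2024 only. Call the estimate 2024 prevalence (2022 census denominator) and delete 2025/2026 from Study procedures. The cost is a wording change.

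Under either route, state when the prevalence analysis is run, so that the reason given for the PMSI year can be checked, and use a newer census count if one has been released by then. A denominator matched on birth cohort, or a multi-year pooled figure, is optional.
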